#### Primary outcome

The Domains of Subjective Extent (DOSE)-Nonadherence 3-item self-report measure will assess the extent of non-adherence to AET over the past 7 days [36].

#### Secondary outcomes

EuroQol-5 Dimension 5 Level (EQ-5D-5L): a 5-item self-report health-related quality-of-life measure, assessing QoL over five components including mobility, self-care, usual activities, pain/discomfort and anxiety/depression [37].

McGill Quality of Life-Revised (MQoL-R): a 14-item self-report measure assessing physical well-being, physical symptoms, psychological symptoms, existential well-being and support, and overall quality of life [38].

Self-Efficacy for Appropriate Medication Use Scale (SEAMS): a modified, 6-item version of the SEAMS self-report measure will be used to assess self-efficacy for medication taking [39].

Self-Report Behavioural Automaticity Index (SRBAI): a 4-item self-report measure assessing habitual behaviour patterns [40].

Beliefs about Medicine Questionnaire (BMQ-AET): a 10-item self-report measure assessing specific medication beliefs on concern and necessity belief scales [41].

Multi-Dimensional Psychological Flexibility Index-Short version (MPFI): a 24-item self-report measure assessing psychological flexibility and inflexibility [42].

Depression Anxiety Stress Scales (DASS-21): a 21-item self-report measure comprising three subscales assessing depression, anxiety and distress [43].

European Organisation for Research and Treatment of Cancer (EORTC) QLQ-C30: a 30-item self-report measure assessing health-related quality of life in cancer patients [44].

EORTC QLQ-BR45: a 45-item self-report measure assessing QoL in patients with breast cancer [45].

EORTC-IL133: a 2-item self-reported measure created from the EORTC item library (https://qol.eortc.org/item-library/), to assess vaginal discharge and abnormal vaginal bleeding.

UK Cancer Costs Questionnaire (UKCC): an adapted version of the UKCC self-report measure to assess services and medications participants may have used while participating in the trial [46].

Adjuvant Endocrine Therapy Use: a 3-item self-report measure, created for the purpose of this trial, asking about AET prescribed, the date of first prescription, previous AET and any reasons for switching at baseline. At follow-up, 3 items will ask about any changes to the AET prescription in the previous four months and reasons for switching AET.

Adherence to Intervention Components: a self-report measure assessing adherence to the intervention components, created for the purpose of this trial. The measure comprises two items for each intervention component they were allocated to receive; asking whether they received the component and how much of the component they used. Participants randomised to the ACT component will be asked two additional questions about how much of the home practice tasks they completed, and how many of the audio files they listened to.

Use of ACT skills: a 4-item self-report measure, created for the purpose of this trial, assesses engagement with ACT skills.

Reconstructive Surgery: a 3-item self-report measure, created for the purpose of this trial, asking about reconstructive surgery, whether breast cancer medication was stopped before or after the therapy, and for how long.

### Participant timeline {13}

Table 3 describes the timeline for the interventions and all trial assessments.

### Sample size {14}

The trial is powered to detect small to moderate (*d* = 0.28) main effects for each intervention component on medication adherence, based on findings from a meta-analysis of 8 AET adherence trials [17]. This is with the intention that the optimised intervention package would result in a moderate to large effect (*d* = 0.50). This would be clinically meaningful with regard to mortality outcomes [13, 14, 47]. We estimate that 512 participants (*n* = 32 per condition) will provide 80% power to detect a main effect of 0.28 assuming a 5% significance level and 20% loss to follow-up. Treatment-related clustering due to ACT therapists was not accounted for in the sample size calculation. Our use of effect coding (− 1, + 1) means that all interactions will also be powered to the same level, assuming the same size of effect. As each comparison corresponds to a distinct hypothesis, no adjustment in significance level will be made for multiplicity. This aligns with the purpose of the trial to optimise a complex intervention rather than definitively evaluate it.

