## Methods: participants, interventions and outcomes

### Study setting {9}

Trial sites will be secondary care NHS Trust hospitals providing services for breast cancer patients. Sites expressing an interest in the trial will be invited to complete a site feasibility questionnaire to verify that the team at the site is willing and able to comply with trial requirements to confirm capacity and capability. We will maintain a summary of participating sites and reasons for non-selection. Participating sites will be required to have obtained local ethical and management approvals and to undertake appropriate training in trial procedures (including a site initiation Q&A and, where relevant, the ACT intervention training) prior to the start of recruitment into the trial. A list of all participating trial sites is available at https://ctru.leeds.ac.uk/roseta/roseta-news/. The ACT component was delivered by therapists working in NHS sites, with two models of delivery whereby the therapist (1) treats patients from the same site the therapist is working from, or (2) treats patients at a different site than their own. 

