## Statistical methods

### Statistical methods for primary and secondary outcomes {20a}

#### Primary endpoint analysis

The DOSE-Nonadherence extent scale will be scored as per author guidance and summarised overall and by factor at baseline and 12 months post-randomisation using descriptive statistics. The primary analysis will use a linear regression model. The four main effects, the eleven interactions (all two-way, three-way and four-way) together with the stratification factors (recruitment route and age group) and the DOSE-Nonadherence score at baseline will be included as independent variables in a single analysis model. This approach is pre-specified and will not be based on estimated interactions. Model fit will be explored and poorly fitting models may lead to additional sensitivity analyses.

Effect coding (− 1, + 1) will be used for every factor in the analysis model to ensure the estimation of main effects rather than simple effects as would be obtained via dummy coding (0, + 1); that is, the average effect of each factor across all levels of the other factors, rather than the effect of a component at a particular level of the other factors.

Type III sums of squares, mean square, and *p*-values will be presented for overall effects; as will the parameter estimates, associated standard error and *p*-value for each covariate. Due to the nature of effect coding, parameter estimates represent ½ the main effect and ½ the interaction effects. Graphical plots (e.g. Pareto plot) will be presented to further explore the main and interaction effects of the intervention components. Participants recruited during the final 4 months of recruitment will have a shorter duration of follow-up (8–11 months). Data from the final planned follow-up for these participants will be included in this analysis.

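### The primary regression has no allowance for ACT therapist clustering, so the p < 0.05 screen is too liberal for the ACT main effect, and 80% power is not shown to hold for that component

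*Protocol article*

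**What the plan says.** Under Sample size {14} the article states that "The trial is powered to detect small to moderate" main effects (d = 0.28) for each component. "We estimate that 512 participants" (32 in each of 16 conditions) are said to give "80% power to detect a main effect of 0.28", "assuming a 5% significance level and 20% loss to follow-up". The same paragraph adds: "Treatment-related clustering due to ACT therapists was not accounted for in the sample size calculation".

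Under Primary endpoint analysis, "The primary analysis will use a linear regression model". Its terms are the four main effects, the eleven interactions, recruitment route, age group and baseline DOSE-Nonadherence score, and the approach is described as pre-specified. The only opening is that a poor fit may prompt extra sensitivity analyses.

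Under Study setting {9}, "The ACT component was delivered by therapists working in NHS sites", treating women from their own site or from another. The Intervention description gives five 25-minute therapist sessions per woman. Under Decision-making, a main effect or interaction with p < 0.05 makes a component important, and coefficients that miss the threshold are set to zero.

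**The concern.** Women treated by the same therapist may have correlated outcomes. Only the ACT-on half of the trial is exposed to this (256 of 512 by allocation), so the data are partially nested: clustered on one side of the ACT contrast and independent on the other. An ordinary regression treats all errors as independent and so understates the variance of the ACT-on mean.

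The p-value is what screens components in or out. If the standard error is too small for ACT only, ACT faces a looser threshold than SMS, leaflet and website, although the plan means to hold all four to the same 5% level. The sentence on clustering in the sample size section covers planning only. It does not touch the analysis, where the standard error is produced.

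**Working it through.** **Inputs from the article.** N = 512; loss to follow-up 20%; two levels per factor with equal allocation; d = 0.28; 5% level (taken as two-sided). Analysed: 512 × 0.8 = 409.6, or n = 204.8 per level of each factor.

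**The article's own figure.** With SD 1 and independent observations, SE = √(2/204.8) = 0.0988. Power = Φ(0.28/0.0988 − 1.96) = Φ(0.873) = 80.9%. In the other direction, 201 per level is 402 in all, and 402/0.8 gives 503, close to 512 = 16 × 32. The stated design reproduces. It takes no credit for baseline adjustment.

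**Adding therapist clustering.** J therapists and the ICC are assumptions, because the article gives neither. Completers per therapist: m = 204.8/J. Design effect on the ACT-on side only: DE = 1 + (m − 1) × ICC. True SE = √((1 + DE)/204.8). The planned model still reports 0.0988.

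- Actual type I error of the planned test: 2 × [1 − Φ(1.96 × 0.0988/true SE)]
- Power of a correctly sized test: Φ(0.28/true SE − 1.96)
- Rejection rate of the planned test at d = 0.28: Φ((0.28 − 1.96 × 0.0988)/true SE)

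Worked case, J = 20 and ICC 0.05: m = 10.24; DE = 1 + 9.24 × 0.05 = 1.462; true SE = √(2.462/204.8) = 0.1096, which is 1.11 times the reported value. Type I error is 7.7%, correctly sized power 72.4%, planned-test rejection rate 78.4%.

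| J | ICC | Reported SE / true SE | Type I error, planned test | Power, correctly sized test | Rejection rate at d = 0.28, planned test |
|---|---|---|---|---|---|
| 10 | 0.02 | 0.92 | 7.3% | 73.6% | 78.8% |
| 10 | 0.05 | 0.82 | 10.8% | 64.2% | 76.3% |
| 20 | 0.02 | 0.96 | 6.1% | 77.4% | 79.8% |
| 20 | 0.05 | 0.90 | 7.7% | 72.4% | 78.4% |
| 40 | 0.01 | 0.99 | 5.2% | 80.1% | 80.6% |
| 40 | 0.02 | 0.98 | 5.5% | 79.3% | 80.4% |

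These are normal approximations; small-sample degrees of freedom would lower the corrected power somewhat further.

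**Simulation.** The effect-coded 2^4 regression with all 15 effects, 410 completers and 4,000 null trials per setting gave ACT type I errors of 7.2% and 11.8% (J = 10, ICC 0.02 and 0.05) and 6.6% and 8.5% (J = 20). The other main effects and the ACT interactions examined stayed between 4.1% and 5.9%. Therapist effects largely cancel from those contrasts when each therapist treats women across the ACT-on conditions.

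**Margin.** 80% requires (2 + (m − 1) × ICC)/204.8 ≤ (0.28/2.802)², so (m − 1) × ICC must stay below about 0.046.

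**Offset from baseline.** The model includes baseline DOSE. If that scales the variance by 1 − r², corrected power at J = 20 and ICC 0.05 becomes 76.3% for r = 0.3 and 83.9% for r = 0.5. The latter is about 81.6% if baseline explains none of the therapist variance: SE = √((0.75 + 0.75 + 0.462)/204.8) = 0.0979. The article gives no baseline correlation.

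**The case against.** The best defence has four parts.

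First, the omission from the sample size is disclosed. That is true, and disclosure is better than silence, but the sentence says nothing about the analysis model.

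Second, therapist clustering could be handled in the unseen statistical analysis plan. The article expressly leaves imputation, subgroups and the prescribing-data model to that plan. It does not leave the primary model to it; it lists the terms and calls the approach pre-specified. An optional sensitivity analysis for poor fit would not change the p-value used for screening.

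Third, the ICC may be small. ACT here is guided self-help, the outcome is self-reported pill-taking over seven days at 12 months, and women who never attend share no therapist effect. This stands as a reason to expect the lower end of the range, but not as a reason to assume zero.

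Fourth, this is an optimisation trial. There is no multiplicity adjustment, interactions are reconsidered after main effects, and a definitive evaluation is anticipated. That tempers the consequence. It does not explain why one component should be tested at a looser level than the other three.

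Three stronger readings are tempting and not supported. A reader might infer that the 80% power is false for ACT; with no ICC or caseload given, and a possible gain from baseline, it is only not shown. A reader might charge the planned regression with both the inflated error and the corrected-test power loss. These belong to different tests: the planned test keeps a rejection rate of about 76% to 80% at J = 10 to 20 and ICC 0.02 to 0.05, at an inflated type I error, while the corrected test holds about 5% and loses power. A reader might also argue that the costliest component would be let in too easily. The article ranks no component costs, and its primary selection criterion sets cost aside.

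**Conclusion.** The concern holds for the analysis, and conditionally for the power. As written, the primary model understates the ACT main-effect standard error whenever the therapist ICC is positive, and the bias is essentially confined to that effect provided that therapists treat women across all ACT-on conditions. The size depends wholly on assumed values. Over ICC 0.02 to 0.05, type I error runs from about 6% to 8% with 20 therapists and 7% to 11% with 10; with 40 therapists and ICC up to 0.02 the problem nearly vanishes. The calculation has less than one percentage point to spare over 80%, so a modest design effect takes a valid ACT test below it unless baseline adjustment compensates. The analysis model should be corrected before any analysis; the power wording is secondary.

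**What to change.** In Primary endpoint analysis, keep the same fixed effects and do one of the following:

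- Make the model partially nested, with a therapist random effect for ACT-on participants only and small-sample degrees of freedom.
- Use cluster-robust standard errors, with ACT-off women as singleton clusters and ACT-on women who never had a therapist treated likewise. Waiting lists and cross-site delivery mean that some ACT-on women may have no identifiable therapist, so a rule that places each woman under an assigned therapist would not always work.

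Confirm that each participant's therapist is recorded. The article lists session summaries and therapist checklists but does not state that link.

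In Sample size {14}, say that the 80% assumes no therapist clustering and so is not shown to hold for the ACT main effect. Give ACT power over a range of ICC and caseload, and note that baseline adjustment may offset some or all of the loss.

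The cost is slightly more analysis work and a less favourable stated power for ACT. No change to recruitment or to the design is needed.

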### Recruitment {15}

Participants will be identified and recruited from UK NHS hospital sites providing services for breast cancer patients. Sites who are recruiting or who are planning to recruit to other trials where the primary aim is to support adherence to AET will be reviewed to determine whether co-enrolment would be feasible in terms of recruitment to target and site capacity. Participants will be identified via four recruitment routes. In Route 1 a research nurse will screen patient records for potentially eligible patients, who will be imminently attending an upcoming appointment. In Route 2, patients who self-refer to their oncologist to discuss problematic medication side-effects and/or adherence within 24 months of completing their hospital treatment will be identified. In Route 3 a research nurse will retrospectively screen patient records for potentially eligible patients who have completed their hospital treatment within the last 24 months. The research nurse will post an invitation letter and information sheet to potentially eligible participants. Route 4 involves the self-referral of potential participants, identified via local breast cancer support groups and charities, targeted social media campaigns, and the Be Part of Research Volunteer Service. Interested participants will be directed to a trial website which contains all trial information and an initial screening questionnaire, which will be sent to the CTRU trial team. If the patient is likely to be eligible based on the initial details provided, the CTRU trial team will send the patient’s details to the relevant hospital site and will make the patient aware. The research nurse will contact potentially eligible participants via telephone. Participating sites will complete a screening form for all identified patients, including anonymised data regarding age, ethnicity, staging, tumour type and whether a patient is randomised. Reasons for non-randomisation will also be captured. For all routes, the research nurse will confirm eligibility and record informed consent, either remotely or in person.

A Study Within A Trial (SWAT) will be embedded to understand the effectiveness and cost-effectiveness of a charitable donation incentive for increasing participant recruitment rates. This recruitment SWAT, sponsored by the University of York, will evaluate the effectiveness of a £10 charitable donation, on an unconditional basis, versus no charitable donation (i.e. the usual invitation) on participant recruitment rates.

## Assignment of interventions: allocation

### Sequence generation {16a}

Participants will be randomised in an equal allocation ratio to one of 16 experimental conditions, ensuring randomisation to relevant levels of factors occurs at the same time point. Randomisation lists will be prepared by the CTRU statistical team using stratified permuted blocks with fixed block size, to ensure experimental conditions will be well balanced for recruitment route (route 1 vs. route 2 vs. route 3 vs. route 4) and age (< 50 and ≥ 50).

### Concealment mechanism {16b}

Randomisation will be performed using the online CTRU-automated 24-h randomisation service which ensures allocation concealment. The service is accessible to trained researchers with an authorisation code and pin.

### Implementation {16c}

Following confirmation of eligibility and informed consent, participants will be registered onto the trial by an authorised member of staff at the research site, using the CTRU automated 24-h registration service. Following registration, the participant will be emailed a link to complete the online baseline questionnaire, and the research nurse will collect baseline data from the participant’s medical records. Once the baseline questionnaire and medical record review have been completed, participants will be randomised by an authorised member of staff at the research site using the CTRU automated 24-h randomisation service.

Following successful randomisation, the person performing the randomisation, the principal investigator, and the relevant local research team at that research site will receive an automated email confirmation of randomisation, highlighting subsequent tasks required for the site i.e. notifying the participant of their allocation with an intervention summary document, and informing the participant’s General Practitioner (GP) of their participation via letter. For participants allocated to the ACT component, a nominated person at the corresponding psychology service will also receive the email notification highlighting that an appointment should be scheduled. For participants allocated to the website or information leaflet components, the research nurse will provide the website link and log-in details and/or the information leaflet one-week post-randomisation via email. The commencement of the SMS component will be coordinated by the CTRU.

## Assignment of interventions: blinding

### Who will be blinded {17a}

Participants, therapists, the research nurse or delegate who performs the recruitment process and the CTRU statistical team will not be blinded to allocation. It is not possible to blind the research nurse or delegate as they inform the participant of their randomisation allocation and coordinate some of the interventions. GPs will be informed about trial participation but will not be informed of a participant’s allocation. Clinical teams will not routinely be informed about randomisation allocation.

The trial design incorporates measures to reduce bias. Follow-up measures will be completed by participants online. Site staff can call participants to aid outcome measure completion and, wherever possible, a member of staff who is blind to the randomisation allocation will conduct these calls. If site staff are subsequently unblinded, subsequent data collection will be completed by an alternative member of the site team who is blind to allocation.

### Procedure for unblinding if needed {17b}

There is no procedure for unblinding, as participants, therapists and the research nurse or delegate performing the randomisation will not be blinded to allocation.

## Data collection and management

### Plans for assessment and collection of outcomes {18a}

#### Baseline assessments

For participants who are eligible and who provide written informed consent we will collect data at baseline and prior to randomisation including mobile phone number, email address, date of birth, postcode, gender, NHS number, marital status, ethnicity, number of children, menopausal status, employment status, education level, co-morbidities, year and stage of diagnosis, tumour type, breast cancer treatment received, endocrine therapy, supportive therapies and previous exposure to ACT/cognitive behavioural therapy or mindfulness. Self-reported participant outcomes described in detail in the outcomes section and Table 3 will also be collected from participants via Research Electronic Data Capture (REDCap).

#### Follow-up assessments

Follow-up assessments will be completed at 4-, 8- and 12-month post-randomisation (Table 3). This includes self-reported participant outcomes, cost data regarding the delivery of the ACT component, and prescribing/dispensing data from NHS England. We will explore the possibility of using NHS England data to conduct longer-term follow-up (i.e. post-12-month randomisation) for participants recruited early to the trial. Participants recruited during the final 4 months of recruitment will have reduced follow-up of between 8 and 11 months. This is to maximise the recruitment period, while adhering to funding constraints. The research nurse will perform a status check for each participant at 4, 8, and 12-month post-randomisation.

